## Abstract

**Background:**

Demographic changes will raise the need for specialized care of older patients. Oropharyngeal dysphagia has recently been declared a geriatric syndrome reflecting its multifactorial background. Alongside multimorbidity, sarcopenia, frailty, and disability, swallowing disorders increase with advancing age, with prevalence rates reported to be as high as 44% in acute geriatric hospital settings and 80% in long-term care facilities. Hence, systematic screening of older patients to diagnose dysphagia and initiate treatment is of paramount importance to prevent bolus death, aspiration pneumonia, and malnutrition and improve quality of life. Several screening tools have been evaluated in emergency and stroke units. However, no published dysphagia screening tool has been validated in the hospitalized, older adult population using a gold standard in dysphagia diagnostics as a reference test. The validation of the proposed test is a first step.

**Objective:**

The Geriatric Bedside Swallowing Screen (GEBS) study aims to validate a new screening tool developed specifically for older inpatients against an instrumental swallowing evaluation, the flexible endoscopic evaluation of swallowing (FEES), which is considered a gold standard. Primary outcomes to be evaluated are sensitivity and specificity for the GEBS in the detection of dysphagia in a mixed older adult population. The presence of dysphagia will be defined by an instrumental swallowing evaluation (FEES), analyzed by the standardized penetration-aspiration scale.

**Methods:**

To validate the GEBS, a prospective cohort study will be carried out. Two institutions, an acute geriatric department and a long-term care facility, will aim to recruit a total of 100 patients aged ≥75 years. After giving their informed consent, patients will undergo the full screening protocol described in the GEBS as well as an evaluation of swallowing function using the FEES. Investigators will be blinded to the results of the respective other testing. The analysis of pseudonymized data sets will be done by a third investigator. Outcomes to be considered are sensitivity, specificity, diagnostic odds ratio, positive and negative likelihood quotient, and the reliability of the proposed dysphagia screening tool using the κ coefficient.

**Results:**

Recruitment started in October 2022 and will end in April 2024. Data publication is planned for early 2025.

**Conclusions:**

If proven to be a valid screening tool for the early detection of dysphagia, further studies including different older adult populations as well as studies to determine the impact of systematic dysphagia screening on parameters, such as rates of aspiration pneumonia or nutritional status, should be planned. Effective screening of dysphagia will lead to earlier detection of patients with impaired swallowing. Those who fail the screening will be referred to speech language pathology for further diagnosis, thus optimizing care while streamlining personnel resources.

**Trial Registration:**

ISCRTN Registry ISRCTN11581931; https://www.isrctn.com/ISRCTN11581931

**International Registered Report Identifier (IRRID):**

DERR1-10.2196/46252

## Introduction

### Background

Due to demographic changes, by 2100, about a third of the population in the European Union will be aged 65 years and older [1]. Medical professions will need to be specialized in the treatment of older patients. This includes the development of efficient diagnostic pathways to ensure optimal care while not overburdening health care systems. Thus, efficient prevention, early detection, and treatment are becoming more important. One important discipline in the care for older patients is *speech language pathology* (SLP), which contributes to the prevention, diagnosis, and treatment of hearing disorders; voice impairments; difficulties with language production; active communication; and swallowing disorders, also known as *dysphagia*.

Dysphagia has been declared a geriatric syndrome by the European Society for Swallowing Disorders, thus highlighting its importance for medical personnel working with older patients. Common causes for dysphagia are stroke, traumatic brain injury, neurodegenerative diseases, as well as surgeries—most commonly following cancer treatment of the mouth and neck. It is important to note that changes to the swallowing process due to aging, which is known as *presbyphagia,* are not considered pathological. If presbyphagia does not cause nutritional decline or the development of aspiration pneumonia, presbyphagia is considered healthy, older-age swallowing [2,3]. If the aging process, specifically the loss of muscle mass within the swallowing muscles, leads to functional deficits and disordered swallowing with pathological consequences without a known neurological or structural cause, it is defined as *sarcopenic dysphagia* [4]. To distinguish between presbyphagia and dysphagia, regardless of etiology, sound knowledge of a healthy, older-age swallowing process is necessary. The loss of muscle mass associated with normal aging, that is, *sarcopenia*, causes *dynapenia,* which is a loss of function and strength within the skeletal muscles [5]. Continual sarcopenia leading to functional decline contributes to the geriatric syndrome known as *frailty,* which is linked to a higher prevalence and worse prognosis for dysphagia [6]. Dysphagia of all different etiologies affects up to 40% of patients in acute hospital settings as well as up to 80% in long-term care facilities [7-9]. The prevalence of sarcopenic dysphagia in older patients admitted to acute hospitals has been determined to be around 30% [10]. As oropharyngeal dysphagia is closely associated with central nervous system diseases, the prevalence for dysphagia in patients with central nervous system diseases is higher as the diseases progress, with estimates of around 85% in older patients [9].

The diagnosis of dysphagia is typically a 2-step process with a clinical swallowing examination by an SLP, who might refer to an instrumental swallowing examination. There are 2 objective instrumental diagnostic tools. The *flexible endoscopic evaluation of swallowing* (FEES) consists of a protocol to evaluate different consistencies of bolus under visual observation of the pharynx and upper laryngeal structures through a transnasal endoscope [11]. The second possibility is a *videofluoroscopic swallowing study*, where a high-resolution x-ray of the mouth and throat produces a video of the whole swallowing process [12]. Since the FEES system is portable, it can be carried out in a bedside setting and does not require as much compliance as the videofluoroscopic swallowing study. The FEES is considered the gold standard in the dysphagia diagnostics of older patients [13].

### Study Goal

As previously described, the identification of patients with impaired swallowing function is of high priority to prevent the occurrence of malnutrition and aspiration pneumonia, as well as bolus death. Considering the demographic changes, routine referral of all newly admitted older patients to an SLP examination will not be feasible. Screening for dysphagia risk has proven to significantly lower pneumonia rates in emergency and stroke units [14-17]. There are several validated screening tools for those populations, for example, the *Gugging Swallowing Screen* [18] or the *Toronto Bedside Swallowing Screening Test* [17], which have excellent sensitivity and specificity for their intended use. Older patients, however, are faced with the challenge of drastically increased time frames for the oral phase of swallowing. This would be a predicator for dysphagia in healthy, younger adults but does not have the same implication in older adults [19].

To search for a screening tool that is validated for an older adult population aged ≥75 years against a gold standard, a systematic review of published screening tools was carried out by the first author, which yielded no results [20]. Of the 40 screening tools that were found (as shown in Table 1), none could be included for further assessment, with the main exclusion criteria being a noninstrumental reference test and a studied population aged <75 years. Some of the studies proposed a new protocol of instrumental swallowing assessments or a clinical bedside swallowing evaluation by an SLP under the term “screening”; those studies were also excluded.

These findings have been replicated by a recent review by Estupiñán Artiles et al [21], as well as the *Arbeitsgemeinschaft der Wissenschaftlichen Medizinischen Fachgesellschaften* (Association of the Scientific Medical Societies in Germany) guidelines for geriatric assessment [22].

**Table 1 table1:** Review of published screening tools.

Exclusion criteria	Screening tools (n=40), n (%)
Reference test	1 (2.5)
Population	8 (20)
Reference test + population	26 (65)
Reference test + population + screening tool	2 (5)
Screening tool + population	3 (7.5)

In accordance with diagnostic study guidelines such as STARD (Standards for Reporting Diagnostic Accuracy) and QUADAS (Quality Assessment of Diagnostic Accuracy Studies), new tests should be validated against a robust reference test, usually the gold standard [23,24]. Following these outcomes, this study aims to fill the gap by validating a specific screening tool—the *Geriatric Bedside Swallowing Screen* (GEBS)—to detect dysphagia in a mixed older adult population aged ≥75 years. The aim is to validate the GEBS using the primary outcome measures of sensitivity and specificity concerning the detection of dysphagia when compared to an instrumental swallowing evaluation.

## Methods

### Test Construction

The starting point for the GEBS was a screening tool already in use at the Department of Geriatric Medicine, Christian Doppler University Hospital, in Salzburg, Austria. It has been demonstrated to be a convenient tool in clinical practice but has never been formally validated. Combined with the results of a thorough review of published evidence on possible reliable predictors for dysphagia, it was developed into a 3-step screening tool. In the first step, 6 risk factors are assessed by observation, patient reports, and chart review (Textbox 1).

Following the assessment of present risk factors and the assurance of patient vigilance, a water swallow test is administered. This consists of swallowing 10 teaspoons of clear water with breaks for voice production and 1 self-administered sip out of a cup. The test is stopped if clinical signs of aspiration such as coughing or wet voice are noted, as well as after the occurrence of one of the following items is noted: breathing difficulties, as a result of the lack of maintaining alertness, head position, or saliva control.

If the water test shows signs of dysphagia and more than one risk factor is present, the third step will be administered, which consists of swallowing a pureed bolus with a consistency of level 4 in the *International Dysphagia Diet Standardisation Initiative* (IDDSI) framework [25]. After making sure that the patient is able to stay awake and upright for 15 minutes; has control over saliva, for example, shows no sign of drooling; and is able to produce voice, several teaspoons of puree are administered with breaks for voice production. The screening must be stopped for decreased vigilance, clinical signs of aspiration, and severe drooling without compensation. Coughing, wet voice, and oral residues are considered indicators for dysphagia.

A point score will be calculated, where a score of 5 points would allow for oral nutrition and medication with pureed food of IDDSI level 4 and thickened liquids of IDDSI level 2 until further examination by an SLP; a score of <5 points would result in the instruction of *nil by mouth* until further examination with a high risk for dysphagia.

This 3-step process of determining risk factors; applying a water-swallow test; and if necessary, administrating a pureed bolus test ensures patient safety while aiming for a high specificity and sensitivity [21,26].

Risk factors for dysphagia.Neurological or neuropsychiatric diseasePneumonia within the last 12 monthsSarcopeniaUnintentional weight lossSymptoms of dysphagia (drooling, wet voice, and coughing)Impaired oral health

### Recruitment

Two Austrian institutions will recruit a total of 100 patients with and without known or suspected dysphagia. One study center is an acute geriatric department, whereas the other is a long-term-care facility. Patients’ inclusion criteria are an age of 75 years or older and the ability to give informed consent. Exclusion criteria are a history of severe brain stroke with a cut-off of 20 points on the *National Institutes of Health Stroke Scale* [27]; a diagnosis of moderate to advanced stages of cognitive diseases defined by 20 points or lower on the *Mini Mental State Examination* [28]; as well as the presence of a tracheostoma with or without dependence on ventilation [29]. Independently of age, these 3 factors are associated with a high prevalence of dysphagia and would be considered too high for risk of bias for the first validation on a mixed older adult population. All patients admitted to the acute geriatric department after the start of recruitment fulfilling the inclusion criteria will be considered and asked to participate in the study. In the long-term-care facility, staff will screen patient data and nominate possible participants, who will then be approached for their consent to participate. Recruitment started in October 2022 with a planned time frame of 18 months.

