## Discussion

### Expected Findings

The GEBS is, to our best knowledge, the first screening tool for the assessment of dysphagia in older patients to be validated against an instrumental swallowing assessment in accordance with guidelines, such as STARD and QUADAS, while taking into consideration individual predisposing factors. This is highly relevant considering the growing demand for personalized medicine in this age group. Similar to children not being small adults in regard to medication, older patients with frailty are to be considered differently for their changed muscle function, metabolism, and physical activity.

This study aims to provide geriatric facilities in the acute setting as well as in long-term care with a reliable, useful tool to screen patients for dysphagia. If the GEBS shows sufficient results to be recommended for broader use in different geriatric settings, further studies in different geriatric settings are advisable. The impact of systematic dysphagia screening with the GEBS should be evaluated by using end points such as rates of aspiration pneumonia, nutritional status, occurrence of bolus death, as well as the patient’s quality of life. Other populations such as patients with moderate to severe cognitive decline or tracheotomy tubes should also be included in further studies, to determine the validity of the GEBS in different patient groups.

Several studies have shown significant changes in the parameters mentioned above, namely pneumonia rates, nutritional status, bolus death, and quality of life, upon systematic screening for dysphagia in emergency departments or stroke units, so there is reason to expect similar effects in geriatric facilities when using a specialized geriatric dysphagia screening tool [14,16].

The screen will be used as a 2-step process in clinical use after having been validated, so the third part will only be administered if no SLP is available. If patients show a risk for dysphagia during the water swallow test and an SLP is available, the screen will be discontinued, and the patient will be referred to an SLP evaluation straight away. Especially in long-term care facilities in Austria, the presence of an SLP is not always the case. Thus, it is necessary for nursing and medical staff to be able to determine the safest method of oral intake until the swallowing function can be assessed by a specialist.

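### Long-term-care participants are nominated by staff under no stated sampling rule, and patients with known dysphagia are not separated, so accuracy may not carry over to the residents to be screened

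*Protocol article*

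**What the plan says.** All in the protocol article.

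- **Recruitment, whole study:** "Two Austrian institutions will recruit a total of 100 patients with and without known or suspected dysphagia". The article gives no split of the 100 by site or by prior dysphagia status.
- **Recruitment, acute geriatric department:** "All patients admitted to the acute geriatric department after the start of recruitment fulfilling the inclusion criteria will be considered and asked to participate".
- **Recruitment, long-term-care facility:** "staff will screen patient data and nominate possible participants, who will then be approached for their consent to participate". No criterion or order for nomination follows.
- **Recruitment, exclusions:** severe stroke, low cognitive score and tracheostoma are excluded as a bias risk, because "Independently of age, these 3 factors are associated with a high prevalence of dysphagia".
- **Intended use:** the Abstract's Conclusions describe the aim with "If proven to be a valid screening tool for the early detection of dysphagia". Study Goal gives the practical reason: "routine referral of all newly admitted older patients to an SLP examination will not be feasible".
- **Outcomes:** sensitivity and specificity are the two main outcomes. Cross-analysis with medical diagnosis, current diet and other variables is to be considered as secondary. Neither site nor prior dysphagia status is named there.
- **Limitations:** only the exclusion of patients with cognitive disease is listed.

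**The concern.** Staff in a care facility know their residents and, under this plan, look through their records before naming anyone. Without a rule for whom to name, nomination may favour residents with evident swallowing trouble and residents with evidently none, leaving out the doubtful ones in between. A screening tool tends to look better in such a sample than among all eligible residents. Nomination may also favour fitter, more cooperative residents, which changes the mix the other way. Since the rule is open, nobody reading the results could tell which happened.

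A second issue concerns the case mix as a whole. A patient whose dysphagia is already established is not one in whom early detection is still to be achieved. If such patients are easier for the screen to flag, one pooled sensitivity says less about unrecognised cases than it appears to. The plan treats case mix as a source of bias when it justifies its exclusions, but states no separate result by prior status.

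**Working it through.** **Plan's own figure.** There is no calculation to reproduce. The Results section says that 100 was chosen without a power analysis, and no expected sensitivity or precision target is given.

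**Model.** Let k be the share of FEES-positive participants whose dysphagia was already known, s1 the GEBS sensitivity in them, and s2 the sensitivity in unrecognised cases. Then

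observed sensitivity = k × s1 + (1 − k) × s2.

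If selection moves k from k0 to k1, the shift is (k1 − k0) × (s1 − s2). If this happens only in long-term care, and that site supplies a fraction f of the FEES-positive patients, the shift is f × (k1 − k0) × (s1 − s2). The documents give none of k, s1, s2 or f; all are assumed below.

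**Step 1: upper bound, selection acting on the whole sample, k from 0.2 to 0.6.**

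| s1 / s2 | At k = 0.2 | At k = 0.6 | Shift |
|---|---|---|---|
| 0.95 / 0.70 | 0.19 + 0.56 = 0.75 | 0.57 + 0.28 = 0.85 | +10 points |
| 0.95 / 0.80 | 0.19 + 0.64 = 0.83 | 0.57 + 0.32 = 0.89 | +6 points |
| 0.90 / 0.85 | 0.18 + 0.68 = 0.86 | 0.54 + 0.34 = 0.88 | +2 points |
| 0.85 / 0.85 | 0.85 | 0.85 | 0 |

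This overstates the case, because the acute department asks all eligible admissions.

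**Step 2: selection in long-term care only, s1 / s2 = 0.95 / 0.70.**

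| f | Known cases favoured, k 0.2 to 0.6: f × 0.40 × 0.25 | Fitter residents favoured, k 0.2 to 0.05: f × (−0.15) × 0.25 |
|---|---|---|
| 0.25 | +2.5 points | −0.9 points |
| 0.50 | +5.0 points | −1.9 points |
| 0.75 | +7.5 points | −2.8 points |

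The Background gives prevalences of up to 40% in acute hospitals and up to 80% in long-term care. With an assumed 50/50 split of the 100, that is 20 and 40 positives, so f = 40/60 = 0.67 and the upward shift is 0.67 × 0.40 × 0.25 = 6.7 points. The exclusions may lower these prevalences.

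**Step 3: the effect of pooling, with no nomination bias.** The pooled figure exceeds sensitivity in unrecognised cases by k × (s1 − s2). With k = 0.2 and 0.95 / 0.70 this is 0.2 × 0.25 = 5 points. It would occur under perfectly consecutive recruitment. It is therefore a reason to report by prior status, and no evidence about nomination.

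**Step 4: scale.** With 40 FEES-positive patients and 36 detected (90%), the exact 95% interval is 0.763 to 0.972. With 80 positives and 72 detected it is 0.812 to 0.956. The shifts in step 2 lie within that uncertainty, but the interval does not account for them, and a larger sample would not remove them.

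The same algebra applies to specificity, with clear non-cases and borderline non-cases in place of known and unrecognised cases.

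**The case against.** The strongest reply is that the text describes an eligibility pre-check. The nomination sentence follows the inclusion and exclusion criteria closely, and staff may simply be reading records for age, cognitive score and stroke history. Nothing says they choose on coughing or diet, so a reader who infers that residents are hand-picked goes beyond the text. The article may also condense a fuller nomination procedure. This stands as far as it goes. But the article does state a rule for each site, and the long-term-care rule leaves out the all-eligible commitment that the acute rule contains. Followed as written, it permits discretion.

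Four other stronger readings are tempting and not supported.

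- **Sensitivity is likely inflated.** The direction depends on whom staff name, which the documents do not say. Step 2 gives either sign.
- **The sample is enriched with known cases.** The phrase "will recruit a total of 100 patients with and without known or suspected dysphagia" can equally mean enrolment regardless of status, and no quota is stated.
- **The plan breaks the guidelines it cites.** The article invokes them for the choice of reference test: "validated against an instrumental swallowing assessment in accordance with guidelines, such as STARD and QUADAS". What they require on sampling is not in the documents, so that argument is not made here.
- **Chart review unblinds the GEBS rater to a known diagnosis.** Chart review is part of the tool and would be available in routine use, and the listed risk factors contain no item for a prior diagnosis.

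It is also fair to say that the study aims at a mixed population aged 75 or over, and that newly admitted patients may include some with earlier dysphagia. Making patients without known dysphagia the main population would therefore be a trade-off, with at most about 100 patients and no extension of recruitment. The point does not ask for that.

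**Conclusion.** The concern holds in a limited form. At one of the two sites the stated selection rule is open to staff discretion, and prior dysphagia status is not separated in the stated accuracy results. Both main outcomes can be affected. With selection confined to long-term care, k rising from 0.2 to 0.6 and sensitivities of 0.95 and 0.70, sensitivity rises by 2.5 to 7.5 points as that site's share of the positives goes from 25% to 75%. If fitter residents are favoured it falls by 0.9 to 2.8 points, and with equal sensitivities it does not move. These figures rest wholly on assumed inputs and show scale only. They do not establish that the trial's result is, or will be, too high. What the documents do support is that, under this plan, the bias could be neither ruled out nor given a sign, and that Limitations does not mention it.

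**What to change.** 1. In the long-term-care facility, replace nomination with a list of all residents who meet the stated criteria. Approach all of them, or take them in random or fixed list order, and log those not approached and those who refuse.
2. Keep the whole sample as the main analysis. Prespecify sensitivity and specificity, with intervals, by site and in patients without known dysphagia at enrolment. Medical diagnosis and current diet are already collected and can define that group.
3. If recruitment at that site can no longer change, name staff nomination under Limitations and restrict the conclusion about long-term care accordingly. Step 2 remains possible.

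The cost is some extra recruitment administration at one site, including a log that is not now described, and wide intervals in the subgroups. With 30 FEES-positive patients and 27 detected, for example, the exact 95% interval is 0.735 to 0.979. The subgroup results should be read as descriptive.
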